### Sample selection and recruitment

Quantitative component: Participant recruitment is purposive and non-probability. Participants are recruited via ALONE, a charity organisation based in Dublin who offer, among other services, a befriending service for older adults. Participants will be recruited from the pool of individuals who contact ALONE to enquire about these befriending services. Typically, such individuals are referred from other services (e.g. GP services) and a visit is arranged to discuss service uptake. For the period of the proposed study data collection, ALONE staff members will include two additional questions to their routine visits – whether individuals self-report as lonely, and whether they would be interested in participating in an evaluation of the services. If individuals wish to be involved, they will receive information followed by a phone call from the project research assistant. If the participant is screened as eligible for the study, and is willing to participate, an initial data collection appointment will be made (with fortnightly appointments to be scheduled following this point for the remainder of the participant’s involvement in the study, up to a total of 11 post-intervention data collection points, or a period of six months).

An average of 35 (range 18–66) individuals were referred to ALONE each month between May 2016 and April 2017 (with a positive trend in numbers, likely owing to increased recruitment efforts on the part of ALONE). Of these, a conservative estimate is that 50% (17) would be interested in receiving a befriending service. A recent evaluation of ALONE’s befriending service found that 40% of service users defined themselves as lonely prior to service uptake (
Burke, 2015). As such, 10 participants can be expected to self-identify as lonely, and thus be considered to be eligible for further screening into the study. Assuming a response rate of 50%, approximately five individuals could be recruited per month, meaning that the target of 85 participants is likely to be reached across 17 months of data collection. Given that six months are required as the follow-up period, this means that a minimum of 23 months’ data collection period is required.

Qualitative component: Participant recruitment is purposive, non-probability sampling, from those already using the befriending service.

Inclusion criteria for quantitative component:
Living in the greater Dublin area.Participants must have contacted ALONE with an interest in receiving befriending services, and must be on a waiting list to receive such services at the time of their trial registration.Participants must be aged 60 and over.Participants must have the ability to provide informed consent.Participants must self-report that they experience loneliness “at least sometimes”.

Exclusion criteria for quantitative component:
Participants must not self-report receipt of a diagnosis from a medical doctor of any of the following: intellectual disability including autism spectrum disorder or psychotic disorder, dementia, serious memory impairmentParticipants must not live further than an hour’s drive from Dublin.

Inclusion criteria for qualitative component:
Participants to be recruited in pairs must have been paired as befriender-befriendee for at least six months, and the befriendee must have been in receipt of any befriending from the service for a minimum of one year.Living in the greater Dublin area.Befriendees must be aged 60 or over.Both pair members must have the ability to provide informed consent.Both pair members must have sufficient language ability to engage in the interview.

### Intervention

The intervention is a befriending service. This service provides companionship to older people who would like extra social contact, through a weekly visit from a volunteer befriender. The volunteer befriender provides companionship and small practical supports where necessary and appropriate. The timing of the weekly visit, along with the nature of these visits (e.g. activities the befriender-befriendee pair may wish to complete together), is agreed between the older person and their volunteer befriender. ALONE recruit volunteers to provide the befriending service. Recruitment, training, and perpetual support is offered by staff at ALONE whose remit is to manage the befriending service. ALONE also have staff members who discuss a range of potential services and benefits available in the community and through ALONE with the older adults who contact them. At this initial meeting, older adults are told about the befriending service and can opt in to receiving this service. If an older adult expresses interest in the befriending service, they are then told about the research study running concurrently with the service. They are told that the service is available to them regardless of whether they are interested in the research study, and that their involvement in the study has no bearing on their receipt of the service. If the older adults are interested at this point in the research study, ALONE staff request verbal consent to pass their contact details to the research team. ALONE befriending service staff contact the older adults to discuss the befriending service with them at this point. They are made aware that the goal is for service users to be matched to a befriender as soon as possible and that before this match takes place at least two observations will be made (one initial, and one after a period of two weeks, and thereafter). If a participant is matched before two observations are delivered, this means that the participant has exited the baseline period of the trial early and their data may be excluded from the final dataset. Participants are asked about any preferences they may have in relation to their befriender by ALONE staff, who then attempt to find a match for them. The befriending match also takes into account location of the service user and potential befriender. Once a match has been made, the service user is informed, and staff from ALONE accompany the befriender to the home of the service user for an initial visit. Adverse events arising from participants’ receipt of the befriending service will be the responsibility of ALONE, as is normal practice.

Receipt of the befriending service intervention is at the discretion of the service user. They are permitted to withdraw from the service at any time if they wish, or request an alternative befriending partner. Should participants withdraw from the befriending service they will be invited to continue with data collection since this will facilitate the examination of ABA (no intervention, intervention, no intervention) phased analysis of the trajectories of outcomes (on an individual basis, with trends rather than inferential statistics being the focus). After completion of the study data collection, it is anticipated that participants will continue to receive the intervention indefinitely, at their discretion.

For the purpose of this study, participants are their own comparators. The reason for this is that the service under investigation is already running in the community and desirable to potential participants. As such it would be unethical to create a control arm as a comparator since these participants would then fail to receive the befriending service that they have requested in good time. The study design permits the research team to measure study outcomes before and after the intervention (befriending service) commences delivery, for a six-month period. As a result, participant outcomes after commencement of the intervention can be compared to those outcomes before this event.

### Adherence

In relation to involvement in the research study, the research assistants will make every effort to be flexible with their appointments for observations, which take place every two weeks. If participants miss observations, the research assistants will provide opportunities for additional observations at the end of the expected 26 weeks, and if this is not possible, and the participant is overly taxed with their engagement in the study, research assistants will suggest that they participate at least in the final time point (after 26 weeks) since our statistical modelling techniques can still garner trends based on these incomplete data. 

No prohibitions are placed on study participants or their befrienders during the trial. Since participants are linked in with general support coordinators over the course of their engagement with the trial, they may be in receipt of other services as requested/required. Support coordinators in ALONE link older adults with a range of nationally available services. The trial ends six months after registration for participants. However, the service persists for as long as participants require or desire. ALONE recommend a year-long commitment in the first instance to befrienders, so in most cases participants will retain their befriending service visits from the same volunteer. However, it is possible that befrienders will withdraw or that participants will request a change in befriender during the trial lifespan. In this event, data collection will continue, and the withdrawal or change in befriender will be modelled as a covariate in the statistical analysis.

### Outcomes

**
*Primary outcome: Changes in health-related quality of life over six months.*
** EuroQOL (quality of life) five-dimension scale with five response levels (EQ5D-5L) (
Rabin *et al.*, 2014). This scale is a well-validated scale of health-related quality of life, measuring five dimensions of health: mobility, self-care, usual activities, pain, and anxiety/depression. The score is suitable for repeated measures and yields scores of five levels of severity for each dimension. Scores can then be combined into a single summary index of utility. A score of 0 on the EQ5D indicates death, while a score of 1 indicates perfect health. The EQ5D-5L is administered at each of 13 observations made two weeks apart for a minimum of two observations before the intervention begins and a maximum of 11 observations after.

**
*Secondary outcome: Changes in brain health over six months.*
** Measurement and definition issues remain in the study of brain health, but most studies exploring this concept rely on either global or domain specific measures of cognitive function which are known to decline in later life, such as memory and executive function (
Wang *et al.*, 2020). Repeated testing of cognitive functioning can result in practice effects, and two strategies are put in place to minimise these. First, specific analytic strategies will be used to detect and account for practice effects in the data. Second, tasks are chosen to minimise the effects of practice on outcomes (
Goldberg *et al.*, 2015). Two alternating versions of the verbal fluency task from the Delis Kaplan Executive Functioning System or DKEFS (
Delis *et al.*, 2001) are available for this purpose, and will be used alternately at observations across 13 timepoints. The DKEFS is a standardised set of executive function tests designed for use across the lifespan. There are nine test in the DKEFS, including the trail making test, the tower of Hanoi test, and the colour-word interference test. Tests from the DKEFS can be used alone, and the verbal fluency task was chosen, because as well as measuring an aspect of brain health (
Wang *et al.*, 2020), as it is a well standardised measure which incorporates an alternate version so that practice effects can be reduced (of key concern in a study design with 13 observations).

**
*Time-varying moderator: Change in loneliness over six months (13 observations).*
** Loneliness is measured using the modified five item University of California Los Angeles (UCLA) loneliness scale (
Russell, 1996) at each of 13 observations made two weeks apart for a minimum of two observations before the intervention begins and a maximum of 11 observations after. In this scale, five items ask participants to rate how frequently they experience each aspect of loneliness, and scores are summed to yield a range of 0-10 (with higher scores indicating more loneliness). The scale is well-validated with high internal consistency (alpha = 0.89) and test-retest reliability (r = 0.73 over two months), and has been used in cohort studies of ageing internationally including the Irish Longitudinal Study on Ageing (
Kenny *et al.*, 2010).

**
*Time-varying covariate: Change in social isolation.*
** The revised Lubben Social Network Scale is a short (six item) and well-validated scale to measure social isolation in older adults (
Lubben & Gironda, 2004). Six questions probe the level of received support from family and friends. Responses are equally weighted and give scores of 0-30 with higher scores indicating more perceived social support/less isolation.

For all above outcomes, change over time is the analysis metric. All outcomes are measured a maximum of 13 times from which trends can be created. Trends will be treated as random effects to account for inter-individual variation and intra-individual variation. All outcomes were chosen with clinical relevance in mind. Befriending services are typically provided because of loneliness so it is crucial to explore whether loneliness typically reduces as a result of uptake in the service. Health-related quality of life and brain health are two of the most critical outcomes for older adults.

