### Sample

Quantitative component: Sample size was calculated to ensure that the study was sufficiently powered. Power in single-case experimental designs is a function of the following: sample size (number of observations per phase multiplied by number of participants), intraclass correlation (ratio of between-case variance to total, or within and between case variance), auto-correlation, effect size to be detected, and the nominal Type 1 error rate (
Shadish *et al.*, 2014a). A rigorous approach described by
Shadish and colleagues (2014a) to calculating sample size uses the alternative d-statistic to the traditional statistic used in between-subjects designs for single case designs. Our primary outcome of interest is health-related quality of life, which will be measured using the EQ-5D scale (see Outcomes). The minimally important difference in this scale has previously been calculated as 0.074 (
Walters & Brazier, 2005) and norms of the EQ-5D have yielded a standard deviation of 0.23 (
Kind *et al.*, 1999). These figures were used to estimate an effect size (using Shadish’s alternative d-statistic) of 0.32. Using this figure in a simulation macro provided by
Shadish and colleagues (2014a), with intraclass correlation set to a conservative estimate of 0.5, autocorrelation set to same, and alpha set to 0.05 for a multiple baseline design) with 13 observations (i.e. a period of six months, specified to be at least two observations in “A” phase, and the rest in “B” phase) per participant, and desired power of 0.8, a sample size of 85 is required. This sample size also provides sufficient power (0.9) for the secondary outcome (brain health), calculated using the same approach described above.

Qualitative component: 10–15 befriendee-befriender pairs will be recruited via the collaborating organisation. Sample size estimation in constructivist grounded theory is guided by data review after 3–4 interviews are conducted to assess thematic saturation (
Charmaz, 2006).

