### Analytic plan

In order to test hypothesis 1, that befriending services will lead to a positive change in health-related quality of life and brain health, two separate generalised additive models will be performed. Data are longitudinal, with 13 time points at which they are collected, before and after a befriending match has been made. The data analysis protocol for the quantitative component of the study is as follows: first, after data collection and audit, visual inspection of plotted data at the individual and group level will be done for both outcomes of interest. Next, pre-intervention and post-intervention trends will be inspected, as well as mean shifts, slope changes, and variability across participants. With respect to verbal fluency as an outcome, data will be analysed for practice effects using published guidelines (
Vivot *et al.*, 2016) and if practice effects are detected, this should be specified in the final model. The modelling of these practice effects is itself of interest and can inform future research attempting to conduct repeated cognitive measures. If practice effects are considerable, this could represent a risk for the interpretability of the results, but since the cognitive outcome is a secondary measure in the study design, this risk does not affect the overall study feasibility. Inferential analyses will be conducted using a generalised additive model (GAM) (
Shadish *et al.*, 2014b) based on a multilevel approach where time points are nested within participants (
Shadish *et al.*, 2014b). This approach is semi-parametric, and calculates autocorrelations from extracted residuals. Time will be scaled such that point 0 is the end of the baseline (two time points of data collection will be conducted during baseline). The GAM approach improves on some key limitations of the multilevel approach, since with the latter, the functional form of the trend must be known, whereas in the former, a smoothing function can be used to model the trend in the data. The moderation effect (investigating whether befriending moderates the impact of loneliness on health and cognitive function) is modelled as an interaction term: the product of the two predictors (loneliness and befriending phase, operationalised as 0 indicating pre-intervention, and 1 indicating post-intervention). This modelling approach will be deployed using the mgcv package in R Studio software (
Wood, 2011).

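### Verbal fluency versions alternate by observation number, but the analysis described names no version term or counterbalanced start, so a version difference can leak into the befriending effect on brain health

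*Protocol article*

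**What the plan says.** Under Outcomes, the protocol article limits practice effects on verbal fluency by using two versions of the task, which "will be used alternately at observations across 13 timepoints". It does not say which version comes first, or whether the order is the same for everyone.

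Under Analytic plan, the befriending effect is a phase indicator, "operationalised as 0 indicating pre-intervention, and 1 indicating post-intervention". It is fitted in a generalised additive model (GAM) in which "a smoothing function can be used to model the trend in the data". Autocorrelation is calculated from residuals. Before modelling, the team will inspect "mean shifts, slope changes, and variability across participants". The only adjustment specific to verbal fluency is for practice: "if practice effects are detected, this should be specified in the final model".

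Baseline length is described in two ways. The Analytic plan says that "two time points of data collection will be conducted during baseline". The Sample section plans "with 13 observations (i.e. a period of six months, specified to be at least two observations in" the A phase, and Intervention and Outcomes also give two as a minimum. Sample selection and recruitment allows "up to a total of 11 post-intervention data collection points".

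**The concern.** Alternation ties version to observation number. With a common starting version and a two-observation baseline, each participant has the second version just before the match and the first version just after it. Version and phase then switch at the same moment.

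Over the whole series the versions almost balance, which suggests that no harm is done. That balance protects a raw before/after mean. A model with a flexible trend works differently: the curve absorbs slow change, so the size of the step is settled largely by the observations close to the match, where version and phase are confounded. A practice curve does not remove this, because practice accumulates over time while a version difference is a saw-tooth.

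At stake is the brain-health half of Hypothesis 1. A difference between test forms could be read as benefit or harm from befriending.

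**Working it through.** **Inputs from the Sample section.** 85 participants, 13 observations, intraclass correlation 0.5, autocorrelation 0.5, alpha 0.05 (taken as two-sided). The design effect size follows from the article's own figures: 0.074 / 0.23 = 0.32. It serves here only as a yardstick. The sample size of 85 comes from a macro that is not shown; it was not reproduced and is not in dispute.

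**Assumptions not in the article.** A version difference δ of 0.1 to 0.3 SD, the same starting version for all, full attendance, and no true befriending effect.

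**Step 1: raw balance.** Code the versions 0, 1, 0, 1, … over 13 observations. With a baseline of two, the share of version 1 is 1/2 before the match and 5/11 after it. The difference is 5/11 − 1/2 = −0.045, so a plain before/after contrast carries 4.5% of δ.

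**Step 2: leak under other models.** The bias in the phase coefficient is δ times the phase element of (X′V⁻¹X)⁻¹X′V⁻¹v. Here v is the version indicator and X holds the intercept, phase and time terms. V has between-person variance 0.5 and within-person variance 0.5, either independent or first-order autoregressive (AR(1)) at 0.5. With every baseline equal to two, the absolute multiple of δ is:

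| Model | Independent errors | AR(1) 0.5 |
|---|---|---|
| Phase only | 0.05 | 0.41 |
| Phase + linear time | 0.08 | 0.58 |
| Phase + quadratic time | 0.64 | 1.30 |
| Phase + linear time + slope change | 1.55 | 1.90 |

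The sign depends on which version is harder and which is given first.

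**Step 3: false positives, all baselines of two.** A penalised spline of time plus phase was simulated with 85 participants and 1500 runs, taking the variance components as known. The ranges cover fits with independent and with AR(1) errors.

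- δ = 0.1 SD: 6-27% rejection.
- δ = 0.2 SD: 20-86% rejection, bias 0.13-0.34 SD in absolute size.
- δ = 0.3 SD: 63-100% rejection.
- δ = 0.2 SD, linear time and correctly assumed independent errors: 5% rejection, so no inflation.

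A separate simulation in mgcv estimated the autocorrelation from residuals (150 replicates per scenario). At δ = 0.2 SD it gave a bias of 0.25 SD and 69% rejection, inside the range above. At δ = 0.1 SD it gave 0.08 SD and 19%.

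**Step 4: varied baselines.** The leak changes sign between a baseline of two and a baseline of three, so mixtures cancel. With equal shares of 2 to 5 observations, the multiple is at most 0.14 in absolute size across the four models in the table. With equal shares of 2 to 6 it lies between about 0.02 and 0.28. In the mgcv simulation at δ = 0.2 SD, 80% of baselines at two gave a bias of 0.16 SD and 37% rejection; baselines spread over 2 to 6 gave 0.06 SD and 10%.

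**Step 5: remedies.** With a version term, the simulated bias is at most 0.015 SD in every model, and rejection is 3-7% when the errors are modelled correctly. Where no version difference exists, the term raises the phase standard error by about 0-9%. Where one does exist it can lower it: in the mgcv simulation with two-observation baselines at δ = 0.2 SD, from 0.12 to 0.08. A 1:1 counterbalanced start gives a multiple of zero.

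**The case against.** The strongest reply is that the article does not fix the conditions for the large figures. It gives no full model formula, and the analysis plan, which is not shown, could contain a version term. It states no common starting version. Three sections treat two baseline observations as a minimum, and match timing depends on preferences, location and the availability of a befriender, so lengths will probably vary. No version difference is reported, and the task is described as well standardised with an alternate form. The article does not say that the fit is weighted for autocorrelation. Plotting the data before modelling might also reveal a saw-tooth.

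Most of this stands as a limit on size. A reader might infer that the plan will produce a spurious jump at the match, with a false-positive rate of 69% or more. The documents do not support that: it needs a common start, baselines of exactly two, a flexible trend and an assumed 0.2 SD difference, all together.

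The reply does not remove the point. The article does set out how repeat-testing artefacts will be handled, and the adjustment it names does not cover the time-patterned factor that its own design introduces. The GAM was chosen so that the form of the trend need not be assumed, which is the setting in which the leak is largest. The Analytic plan itself gives a two-point baseline, and Intervention aims for matching as soon as possible, so short baselines are plausible. A later analysis plan could add a version term, but it could not change the starting version already given to the 49 participants recruited.

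**Conclusion.** The point holds in conditional form. If participants share a starting version and most baselines have two observations, a version difference can leak into the phase coefficient under a flexible trend, in either direction. The leak is about 0.6 to 1.3 times the difference with a quadratic trend and only 0.05 to 0.08 in phase-only or linear models with independent errors. As a yardstick, the bias of 0.13-0.34 SD found at an assumed 0.2 SD difference is comparable with the design effect of 0.32. With well-spread baselines the problem is modest (about 10% rejection at 0.2 SD; with 150 replicates the 95% interval is roughly 6-16%). With a counterbalanced start it disappears.

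Only the secondary outcome is concerned. The change is worth making because it protects the brain-health result in all these scenarios at almost no cost.

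**What to change.** In the Analytic plan, add the version administered at each observation as a two-level fixed factor in the verbal fluency GAM, separate from any practice-effect term. State the starting-version rule used so far and, for participants still to be enrolled, alternate which version is given first.

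The version factor is the essential part. If the 49 participants already recruited all began on the same version and the remaining 85 − 49 = 36 are split 18/18, the net imbalance is (67 − 18)/85 = 0.58. Late counterbalancing alone would then leave more than half of the leak, given similar baseline lengths in both groups.

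The cost is one degree of freedom, one sentence in the plan and a phase standard error up to about 9% larger if the versions prove equivalent. No new data are needed, provided that the version given was recorded at each observation.
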